### Implementation in the Field

The last project phase consists of the CDSS implementation in the field and a prospective study following a strict protocol that will be elaborated according to Tanzania laws on human research. The goal will be to observe the relevance of the generated reports for the clinicians in Tanzania. KIDH will select a cohort of clinicians actively involved in TB treatment with rifampicin that will identify patients to enroll in the study. This step will assess the benefit of CDSS use versus standard practice in Tanzania. Thanks to the existing network of KIDH, we expect to have at least 30 patients in the cohort treated in 10 facilities in the field.

Before introducing TuberXpert to the clinicians, the selected panel will follow their patients according to standard clinical management while collecting all the needed information for a TDM procedure using a dedicated form that will be elaborated according to CDSS specificities. In addition, the possible dosage adjustments, the patient’s health status evolution (ie, clinical features and pragmatic microbiology parameters), and all other relevant data about the patients will be collected. Blood analysis will be implemented and centralized at Kilimanjaro Clinical Research Institute (KCRI) or at KIDH. The KIDH will use this information to feed the CDSS to determine the correspondence between the CDSS output and the clinicians’ decisions. The CDSS will be used in this phase without interfering with the patient’s treatment.

Then, the consortium will train the clinicians in the field about CDSS usage and report interpretation. This training will not only be beneficial for this project but also for spreading the TDM culture throughout Tanzania.

After the training session, the CDSS will be available at the clinics participating in the study. We will deploy the software in facilities where such deployment is feasible, in a setup that still has to be defined, and also set up a direct communication channel with the Swiss team to help the clinicians with any questions regarding software usage or TDM in general. More clinicians will be involved in this second phase, including but not limited to those who participated in the previous non-CDSS phase, as participation in the first phase is not mandatory to be part of the second one. The study protocol will be written during the project and will strongly focus on the clinical relevance of the CDSS and the acceptance of the software tool [28]. The clinicians will be asked to collect the same information as in the first implementation phase, including clinical features during the patients’ follow-up and pragmatic microbiology parameters. Likewise, we will establish the baseline information on the safety of TDM by observing and assessing patients’ clinical evolution between the 2 phases, which will subsequently offer the opportunity to determine the overall benefit of CDSS-assisted versus standard patient management in Tanzania. This second part will also help identify the cases where TuberXpert has influenced the clinicians, why they would not be keen to follow the suggested regimens, and if the outcome of the dosage adjustment has been positive for the patient. If clinicians scarcely follow the CDSS suggestions, we will investigate the barriers and bottlenecks that hinder its implementation to increase the accessibility of benefits of the TuberXpert technology. The analysis will then be performed by comparing the subgroup of clinicians who followed the CDSS recommendations versus those who were reluctant and included in the first phase to assess the CDSS benefits. The research question component is—are clinicians keen to adhere to the suggestions of an automated CDSS?

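### CDSS benefit is to be judged by comparing clinicians who followed the recommendations with those who were reluctant, so selection can create or hide a benefit

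*Protocol article*

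**What the plan says.** All of this is in the protocol article, Methods, Implementation in the Field.

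- **Aim.** "This step will assess the benefit of CDSS use versus standard practice in Tanzania".
- **Design.** Clinicians first manage patients in the standard way while data are collected. They are then trained and given the CDSS, and collect the same information again. Nothing is randomised: "KIDH will select a cohort of clinicians actively involved in TB treatment with rifampicin that will identify patients to enroll in the study".
- **Changing participants.** More clinicians join the second phase, and "participation in the first phase is not mandatory to be part of the second one". On sites: "We will deploy the software in facilities where such deployment is feasible".
- **Between-phase look.** Patients' clinical evolution is to be assessed across the two phases, "which will subsequently offer the opportunity to determine the overall benefit of CDSS-assisted versus standard patient management in Tanzania".
- **Stated analysis.** The one sentence that says how the analysis will be performed describes "comparing the subgroup of clinicians who followed the CDSS recommendations versus those who were reluctant and included in the first phase". Its purpose is explicit: the sentence ends "included in the first phase to assess the CDSS benefits".
- **Reasons for not following.** The second phase is also to establish "why they would not be keen to follow the suggested regimens, and if the outcome of the dosage adjustment has been positive for the patient".

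**The concern.** Whether a clinician follows a recommendation is settled after the CDSS is introduced. It can depend on how ill the patient is, on comorbidity, on the size of the suggested change, on the clinician's skill and on the facility's resources. Each of these may also affect outcome. The article itself expects not following to have causes, since it plans to study them, and its Introduction says comorbidities raise the risk of unfavourable outcomes. A difference between followers and reluctant clinicians therefore mixes any CDSS effect with the reasons for following.

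Three features add to this:

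- The comparator does not match the aim. A reluctant clinician in the second phase has been trained and has the report, which is not standard practice.
- The first-phase condition attaches only to the reluctant group. Followers may be newly joined clinicians or sites.
- Following is a decision made for each recommendation, but the sentence labels whole clinicians. A clinician who follows some recommendations and not others has no defined group.

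At stake is whether a reported CDSS benefit, or its absence, can be believed.

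**Working it through.** **1. There is no plan figure to reproduce.** The section expects at least 30 patients in 10 facilities, on the strength of an existing network. It gives no effect size, outcome rate or power, so every rate below is an assumption.

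**2. Possible readings of the sentence.**

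| Reading | Consequence |
|---|---|
| Comparator is reluctant clinicians who also took part in the first phase | Comparator is selected twice and has CDSS access |
| Comparator is reluctant clinicians plus first-phase care | CDSS-exposed patients are counted as standard care |
| Analysis applies only if few recommendations are followed | Followers are a small and highly selected group |

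Under every reading the CDSS group contains only those who chose to follow.

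**3. Size of a false effect when following varies by patient.** Assume no CDSS effect, half the patients with good prognosis (85% favourable) and half with poor prognosis (50%). Let g and p be the probabilities of following in the two halves.

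- Followers' rate = (0.5·g·0.85 + 0.5·p·0.50) / (0.5·g + 0.5·p)
- Non-followers' rate: the same with 1−g and 1−p

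| g, p | Followers | Non-followers | False difference |
|---|---|---|---|
| 0.6, 0.5 | 0.380/0.55 = 69.1% | 0.295/0.45 = 65.6% | +3.5 points |
| 0.7, 0.4 | 0.3975/0.55 = 72.3% | 0.2775/0.45 = 61.7% | +10.6 points |
| 0.8, 0.3 | 0.415/0.55 = 75.5% | 0.260/0.45 = 57.8% | +17.7 points |

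Exchanging g and p (poor-prognosis cases followed more often) gives the same sizes with a negative sign.

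**4. Same point in terms of case mix.** Observed difference = true effect + (qF − qR) × (pHigh − pLow). Here qF and qR are the good-prognosis shares among followers and reluctant, and pHigh and pLow are the favourable rates.

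- 90%/70%, no true effect: shares of 60% v 40%, 70% v 30% and 80% v 20% give +4, +8 and +12 points.
- 90%/50%, no true effect: the same shares give +8, +16 and +24 points.
- True effect +8 points, shares 30% v 70%: observed 8 + (−0.4 × 20) = 0 with 90%/70%, and 8 + (−0.4 × 40) = −8 with 90%/50%.

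A benefit can thus be created, hidden or reversed. If the shares are equal the bias is zero.

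**5. Continuous outcome, by simulation.** With 20,000 runs of 30 patients, a correlation of +0.3 between prognosis and following gives a false +0.48 SD. A correlation of −0.3 reduces a true +0.5 SD to 0.02 SD.

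**6. Precision.** If 30 patients were divided between the groups and the favourable rate were 80%, the 95% half-width is 1.96 × √(0.16/n1 + 0.16/n2): 29 points for 15/15, 30 for 20/10 and 36 for 24/6, before any allowance for clustering. Such data could neither show nor exclude biases of the sizes above.

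**The case against.** **It is not the only look at benefit.** A reader might infer that the follower contrast is the only benefit analysis planned. The documents do not support that: the same section mentions comparing patients' evolution between the two phases to determine overall benefit. What stands is that this is described as an opportunity, while the contrast by adherence is the one stated as the analysis.

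**Roll-out does not hang on it.** A reader might also infer that extension to other countries depends on this contrast. Future Directions makes possible deployment elsewhere conditional on positive conclusions in general, covering adherence and impact. The abstract's conclusions say the system will be proposed to other countries without that condition.

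**Adherence is the research question.** The section closes by asking whether clinicians will adhere, and the abstract describes the field study in those terms. Comparing followers with reluctant clinicians suits that question. But the sentence gives its purpose as benefit, and the section's aim also includes benefit.

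**The sentence may be conditional, and the field protocol is unwritten.** It follows directly on the case of scarce uptake. Selection remains on that reading. The pending protocol makes correction easy but does not make the stated contrast sound.

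**The illustration is at patient level.** This is fair. The plan groups clinicians, so prognosis produces bias only to the extent that case mix differs between following and reluctant clinicians, and that gap was not estimated. Differences in skill and resources between clinicians would add bias of their own. No binary favourable outcome is defined in the article either.

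**The alternative is also non-randomised.** True: a between-phase comparison is before/after, with time, training and the Swiss support channel all changing. It at least addresses the stated question and does not sort patients by a later choice.

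**Conclusion.** The point holds as a defect in the stated benefit analysis. Comparing followers with reluctant clinicians does not estimate CDSS use against standard practice under any reading of the sentence, and selection can push the result in either direction. The direction and size in this study are unknown. The false differences of 3.5 to 17.7 points rest on assumed outcome rates, assumed following probabilities and patient-level following. They show what selection can do and do not predict what it will do here.

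The finding does not extend to the whole field phase. A more suitable comparison is already mentioned and needs to be made the benefit analysis.

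**What to change.** In the field-phase protocol:

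1. **Benefit analysis.** Replace the follower-versus-reluctant sentence with a between-phase comparison: all second-phase patients, whether or not the recommendation was followed, against first-phase patients, restricted to facilities (ideally clinicians) present in both phases. Make a simple allowance for facility. With an expected 30 patients in 10 facilities, about 3 each, a list of patient covariates is not workable.
2. **Adherence analysis.** Report followed versus not followed for each dosing decision, with reasons, as a description of adherence and barriers. Label any outcome contrast by adherence as exploratory and not evidence of benefit.
3. **Limits to state.** Time trends, training and the support channel change along with CDSS availability.

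**Cost.** This is a wording change and needs no new data items, because both phases are to collect the same information. The estimate will be diluted where recommendations are not followed. Newly joined sites or clinicians drop out of the main comparison, though they can still be described. Precision will be low if the cohort is near 30 patients.

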### Patient and Public Involvement

The development of this protocol aligns with the patient-centered care approach [29]. This project was designed based on the results of a series of TB research studies in Tanzania that showed individual patients with TB differ and may need different treatment strategies and duration due to variations of disease severity and comorbidities [30-34]. Findings from the described project will be shared with organizations involved in TB management for further refinement before subsequently contributing to shaping the agenda of effective integration of communicable and noncommunicable diseases for policy makers.

### Ethical Considerations

The patient enrollment has been approved at the local health research committee serving Kibong’oto Infectious Diseases Hospital and National Health Research Committee with reference KNCHREC003 and NIMR/HQ/R.8a/Vol.IX/2988. Furthermore, the Ministries of Health and Regional Administrative and Local Government Authority have endorsed implementing this protocol. Dissemination will be done mainly through scientific publications for all project parts. Social media will also be used to gain more visibility. Finally, spreading the usage of the system is a goal envisioned at the end of the project.

## Results

The TuberXpert project started in November 2022. During its first phase, and as of July 2024, a total of 50 patients have been enrolled to gather the required data to build a popPK model for rifampicin. In addition, the panACEA consortium agreed to share and already provided individual rifampicin data collected in three different studies (trial numbers NCT01392911, NCT00760149, and NCT01785186), allowing preliminary popPK model development based on these data. A review of TDM practices for TB treatment in Tanzania has also been conducted within the same timeframe. From January to December 2023, we carried out the report design study. We started with a literature review concerning the best way to present information to clinicians. Then we created mock-up reports and conducted a qualitative study with 2 rounds of interviews (13 Tanzanian and 27 non-Tanzanian clinicians) to end up with the final report layout. In September 2023 we started to CDSS general architecture. In July 2024 the first prototype of the CDSS core system was finalized.

## Discussion

### Principal Findings

The TuberXpert project is a multidisciplinary study blending information technology, clinical expertise, and modeling approaches to deploy precision pharmacotherapy of first-line anti-TB medicine through dosage optimization in TB treatment, thanks to an automated CDSS system. To the best of the authors’ knowledge, there is no existing system offering the same functionality. Some TDM software are available, but they require specific skills and do not end up with a fully automated report generation.

After 18 months, interesting information emerged from the project’s first phases. As seen in other low-resource settings, TB in Tanzania is complicated by socioeconomic factors, comorbidities, and a rigid health care system unsuited to patients who are dual-diseased. Significant pharmacokinetic variability of rifampicin between and within subjects further complicates TB management, potentially leading to unfavorable treatment outcomes. Hence, TDM stands as a considerable asset for addressing the limitations of the generalized “one-size-fits-all” approach by tailoring treatment to patient characteristics. While this personalized approach is appealing, the highly complex pharmacokinetic profile of rifampicin significantly complicates straightforward TDM for nonexpert clinicians. Implementation of TDM is further hindered by features exacerbated by low-resource settings, such as logistical barriers, lack of funding, analytical equipment, or trained pharmacologists suited to TDM. If well implemented in the Tanzanian health care landscape, a CDSS coupled with TDM can provide a practical medical tool facilitating personalized medicine in resource-limited settings contributing to alleviating the TB burden.

The report study emphasized the importance of designing accessible and engaging medical reports, particularly in the context of TDM and CDSS. Simplifying and standardizing report formats can improve comprehension and action ability for clinicians, especially those who are nonexperts. As the TuberXpert project aims to create user-friendly TDM reports for TB treatment, it highlights the necessity of clear visuals and appropriate terminology. Interviews with health professionals revealed that simplicity, clear structure, and effective visuals are crucial, though balancing detailed information with simplicity remains challenging. The study also addressed the complexities of multinational collaboration, stressing the need for consistent and understandable communication across diverse health care environments.

### Future Directions

In July 2024 the team will start with the development of the popPK model based on the acquired data and in parallel prepare and validate the CDSS. These phases are expected to last a year. Finally, the implementation of the system in the field will enable the team to assess the adherence of the clinicians to the proposed adjustments and to observe the real impact of the TuberXpert setup. Shall the conclusions be positive, the system could be deployed in other countries, and extended to other medical drugs.

### Strengths and Limitations of This Study

To our knowledge, this is the first study to investigate the application of CDSS technology at varying health care delivery systems levels to guide TDM in patients with TB in TB-endemic settings, especially where pharmacologists are not available. In the future, routine implementation of TDM-CDSS, particularly for rifampicin, a backbone for TB treatment, is expected to transform TB’s clinical management in resource-limited settings. Anti-TB dosage optimization will improve treatment outcomes of patients who would otherwise succumb or develop drug-resistant TB because of suboptimal drug exposure. This will considerably contribute to the end TB strategy, particularly with arduous forms of TB with either HIV coinfection or coexistent DM or malnutrition.

While the project’s expected impacts are important, some limitations could arise. A lack of computer infrastructure in health facilities may prevent the implementation of a centralized system in resource-limited countries. If such computers are not available, if the network is stable enough, we envision using smartphones thanks to a web server offering the TuberXpert service.

### Conclusions

This game-changing transdisciplinary 3-year project combines technology and pharmacometrics to enable appropriate dosages of anti-TB drugs in patients with TB at various levels of the health care system in TB-endemic settings. TuberXpert thus provides an unprecedented opportunity to optimize and individualize the clinical management of patients with TB in resource-limited settings. Moreover, TDM tends to be increasingly recommended, particularly for treating multidrug-resistant TB with second-line chemotherapeutic agents, when achieving effective and safe concentration exposure is of vital importance [35]. In the end, TuberXpert could be adapted beyond rifampicin and holds promise far beyond TB alone, with indirect benefits in other therapeutic areas such as HIV, cancer, and so forth. At the project half-life, it is too early to draw definitive conclusions, but a set of contributions are expected, for the field of dosage adjustment, TDM, and especially for the patients.

### Contribution to the Field

Findings from this project will provide broad knowledge on the feasibility and appropriateness of dosage correction for individuals with suboptimal drug exposure to medicinal drugs critical for the treatment of a life-threatening condition. The project will concretely validate a model-based dosage adjustment of rifampicin in patients with TB. Through publications, it will enhance evidence-based information applicable in different countries.

Routine implementation of the TDM-CDSS particularly for rifampicin, which is a backbone for TB treatment, will transform the clinical management of TB. The current WHO rifampicin dosage of 10 mg/kg was designed rather empirically without prior evidence derived from preclinical or clinical trials [36]. Researchers have documented rifampicin suboptimal drug levels in at least 50% or more of the TB-treated population [30,37]. However, there is limited evidence on the use of technology to address the gaps [8]. This project will also improve the education of medical doctors in Tanzania concerning the dosage adjustment of rifampicin. The expertise will be made available in remote areas where there is a considerable number of patients with TB.

### Contributions to Patient Care, Disease Management, and Public Health

The project will contribute considerably to the end TB strategy by improving patients’ treatment, particularly with arduous forms of TB (either with HIV coinfection or coexistent DM or malnutrition). It might definitely improve treatment outcomes of patients who would otherwise succumb or develop drug-resistant TB as a result of suboptimal drug exposure [22]. A priori dosage recommendations made in this project as a function of specific patient’s characteristics will already limit the use of dangerous subtherapeutic doses in these fragile populations. Furthermore, TDM can decrease the occurrence of adverse drug reactions in patients by favoring appropriate dosages and preventing overdoses [38]. This project challenges the status quo of empirical treatment toward individualization of therapeutics, a patient-centered approach regarded as an important arsenal for the end TB strategy [39].

### Contribution Toward Implementation of TDM-CDSS as an Innovative Technology

The TuberXpert project fosters collaborations with African or European countries that will enable Tanzania to produce high-quality research on pharmacotherapy while strengthening research capacity, and Switzerland will benefit as well on innovation, science, and entrepreneurship. The proof-of-concept will pave the way to a user-friendly TDM-CDSS that has a good chance of proving applicable to other medicinal drugs.

### Contribution Toward the Community of TDM Users

At the end of the project, the source code of the CDSS and report generator will be publicly available, with a license allowing to use it for nonprofit purposes (possibly to use it for helping clinicians, but not to sell a software). If at some stage in the future a company is interested in commercializing a software embedding parts of the existing source code, a specific license with royalties will be considered as an option for further closed-source exploitation. Both the core engine and the GUI of Tucuxi are available in Open Source [40]. The result of TuberXpert will be proposed within this framework to help as many institutions and countries as possible. The vision is to build a community of institutions revolving around TDM, with participants from various countries able to take advantage of each other to improve patient care. This will be of particular interest to African countries that could have access to such tools for free.

